### Statistical analysis

All statistical analyses will be performed using Stata version 18 (StataCorp, USA). The threshold for statistical significance in this study is set at 5%. As two primary outcomes are measured, a corrected *p* value threshold of 0.025, obtained using the Bonferroni correction technique, will be utilised when assessing these outcomes. Intention to treat analysis will be performed in all cases. Categorical variables will be displayed as frequency (percentage) and analysed using chi-squared test. Continuous variables will be assessed for normality using the Shapiro–Wilk test. Normally distributed data will be displayed as mean ± standard deviation and analysed using unpaired *t*-test. Continuous data that is not normally distributed will be displayed as median (range) and analysed using Mann–Whitney *U* test. Nonadherence to randomly assigned treatment may mean that the intention to treat analysis may misrepresent the true treatment effect. Therefore, a per-protocol analysis will be performed if there is greater than 10% crossover between groups. We do not plan on undertaking an interim data analysis due to the small sample size of the trial and the use of two routine clinical interventions.

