#### Primary outcomes

The primary outcome of interest is the dynamic pain score at 3 and 24 h postoperatively. These scores are measured using a numerical pain scale from zero to ten.

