### Sample size calculation

We performed a retrospective case note review to determine the effect size required. As we had two primary outcomes, the larger of the two sample size calculations was utilised. Sample size calculation was then performed using G*Power (Düsseldorf, Germany) with two-sided significance level of 0.05 and 80% power. The sample size required to detect a mean difference in pain scores of 0.8 at 3 h postoperatively was 26 in each group, whereas that required to detect a mean difference in pain scores of 3.3 at 24 h postoperatively was 20 in each group. Accounting for 30% dropout or non-adherence rate, we arrived at a final sample size of 35 in each arm.

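### The fixed Bonferroni threshold on the two primary outcomes is valid, but Holm's step-down test has more power at the same 5% family-wise error

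*Protocol article*

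**What the plan says.** Under Primary outcomes, the protocol article states: "The primary outcome of interest is the dynamic pain score at 3 and 24 h postoperatively". It treats these as two primary outcomes throughout.

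Under Statistical analysis, the general rule is "The threshold for statistical significance in this study is set at 5" per cent. For the two primary outcomes there is a corrected threshold of 0.025, "obtained using the Bonferroni correction technique, will be utilised when assessing these outcomes". The same 0.025 applies to each outcome whatever the other shows. The article gives no step-down, hierarchical or alpha-recycling rule, and does not say whether success means one significant outcome or both.

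Under Sample size calculation, each outcome was sized "with two-sided significance level of 0.05 and 80% power", that is, without dividing alpha. The number needed to "detect a mean difference in pain scores of 0.8 at 3 h postoperatively was 26 in each group", and the number needed to "detect a mean difference in pain scores of 3.3 at 24 h postoperatively was 20 in each group". "As we had two primary outcomes, the larger of the two sample size calculations was utilised", and an allowance of 30% for dropout or non-adherence led to 35 per arm.

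**The concern.** With two primary hypotheses, plain Bonferroni is never more powerful than Holm. Holm compares the smaller p-value with 0.025 and, if that is significant, the other with 0.05. Suppose p = 0.010 at 24 h and p = 0.035 at 3 h. The written rule claims 24 h only; Holm claims both, under the same 5% family-wise guarantee.

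At stake is power for each outcome separately and for claiming both. This matters more than usual here because the calculated 26 per group gives 80% power at 0.05 and not at the 0.025 used in the analysis. Part of that loss can be recovered in the analysis without enrolling anyone else.

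**Working it through.** **Inputs.** From the protocol article: differences of 0.8 (3 h) and 3.3 (24 h); 26 and 20 per group; two-sided 0.05 and 80% power for sizing; 0.025 per outcome for testing; 1:1 allocation; 30% allowance; 35 per arm. Not stated, hence assumed: the SDs (back-solved below) and the correlation between the two scores (0 to 0.7 tried, 0.3 to 0.5 used for the headline figures).

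**1. Reproduce the plan's figures.** Two-sample t-test, noncentral t with 2n − 2 degrees of freedom and noncentrality d√(n/2):
- 3 h: d = 0.80, alpha 0.05, 80% power gives n = 26 (power 80.7%). Any d from 0.792 to 0.809 gives 26, so the implied SD is 0.8/0.809 = 0.99 to 0.8/0.792 = 1.01.
- 24 h: n = 20 implies d from 0.909 to 0.934, so the SD is 3.3/0.934 = 3.53 to 3.3/0.909 = 3.63. I use d = 0.909.
- Threshold: 0.05/2 = 0.025. Correct.

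**2. Power of each outcome at the two alphas** (exact noncentral t):

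| Analysed per arm | 3 h, alpha 0.05 | 3 h, alpha 0.025 | 24 h, alpha 0.025 |
|---|---|---|---|
| 24 (35 × 0.7 = 24.5, rounded down) | 77.4% | 67.5% | 79.4% |
| 26 | 80.7% | 71.6% | 83.0% |
| 35 | 91.0% | 85.2% | 93.2% |

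At 0.025, 80% power would need 31 per arm for 3 h and 25 for 24 h.

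**3. Error control under Holm.** If both nulls are true, any rejection needs the smaller p-value to be below 0.025, which has probability at most 2 × 0.025 = 0.05. If one null is true, a false rejection needs that outcome's p-value to be below 0.05, which has probability at most 0.05. Neither step uses the correlation. Simulation at 26 per arm agrees: with both nulls true, 5.0% (correlation 0) and 4.6% (correlation 0.5), identical for the two methods; with only the 24 h null true, Holm's error is 4.1% to 4.3%.

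**4. Power under Holm.** For 3 h:

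power = P(p3 < 0.025) + P(p24 < 0.025 and 0.025 ≤ p3 < 0.05).

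Hand check at 26 per arm with independent scores: 0.716 + 0.830 × (0.807 − 0.716) = 0.716 + 0.076 = 0.79. Simulation gives 0.790.

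Simulation with 200,000 trials per setting and unpaired t-tests (Bonferroni → Holm):

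| Per arm | Correlation | 3 h | 24 h | Both | At least one |
|---|---|---|---|---|---|
| 24 | 0.3 | 67.5 → 74.9% | 79.6 → 83.9% | 56.9 → 68.6% | 90.2%, unchanged |
| 24 | 0.5 | 67.5 → 74.7% | 79.3 → 83.0% | 59.1 → 70.0% | 87.7%, unchanged |
| 26 | 0.3 | 71.6 → 78.8% | 82.9 → 86.9% | 62.0 → 73.3% | 92.5%, unchanged |
| 26 | 0.5 | 71.4 → 78.3% | 82.9 → 86.3% | 64.0 → 74.3% | 90.3%, unchanged |
| 35 | 0.3 | 85.2 → 90.2% | 93.2 → 95.5% | 80.5 → 87.8% | 97.9%, unchanged |
| 35 | 0.5 | 85.1 → 90.1% | 93.2 → 95.2% | 81.4 → 88.3% | 96.9%, unchanged |

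A separate run of 40,000 trials per setting gave 62.5% → 73.2% and 64.2% → 74.7% for both outcomes at 26 per arm (correlations 0.3 and 0.5), so about 62–64% → 73–75% overall. The last column cannot change, because Holm's first step is also at 0.025.

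**5. Dependence on the 24 h effect** (26 per arm, correlation 0.4, 3 h power, Bonferroni → Holm):
- 24 h d = 0.5: 71.5 → 73.4%
- 24 h d = 0.25: 71.4 → 71.7%
- 24 h d = 0: 71.6 → 71.8%

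In these cases it is the 24 h outcome that gains more, for example 32% → 40% at d = 0.5.

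**The case against.** The strongest objection is that nothing here is wrong. The plan names two primary outcomes, prespecifies a correction and computes the threshold correctly; Bonferroni is a conventional, conservative choice. That stands, so the point is an efficiency improvement only. Bonferroni's conservatism also buys something: its 97.5% confidence intervals always agree with its tests, which Holm cannot promise for an outcome passed at 0.05.

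Three stronger readings are tempting, and the document supports none of them.

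- *The trial is already short of power at 3 h.* This is true at the calculated 26 per arm and at 24 evaluable per arm, but not at the 35 randomised, where Bonferroni gives 85%. The article analyses by intention to treat and expects high retention (Patient population; Recruitment, enrolment and randomisation). On numbers alone, power falls below 80% only if more than 35 − 31 = 4 per arm lack data. Non-adherence could still dilute the effect.
- *Holm makes a positive trial more likely.* The chance of at least one significant primary outcome is the same under both rules, and the article does not require both.
- *Holm cures the sample size problem.* At 26 per arm it reaches 78% to 79%, still under 80%. The cause is sizing at 0.05 and testing at 0.025, which is a separate point.

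The objection on timing also stands. Recruitment was expected to finish in August 2025 and the article appeared in September 2025, so this changes the primary decision rule late. It needs a documented amendment and not merely an edit.

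**Conclusion.** The concern holds as an optional, low-cost improvement. The fixed 0.025 rule is valid but uniformly less powerful than Holm at the same 5% family-wise error. That ordering needs no assumption about SDs, correlation or effect sizes, and holds for any valid p-values, including Mann–Whitney.

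The size does rest on assumptions. Under the implied effects and a correlation of 0.3 to 0.5, Holm adds 5 to 7 points of power at 3 h, depending on the number analysed, and about 10 to 11 points for claiming both outcomes at 26 per arm. At 26 it recovers about 7 of the 9 points lost at 3 h (80.7% to 71.6%). If the 24 h effect is d = 0.5, the 3 h gain is about 2 points; near zero, it is almost nothing.

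**What to change.** By a dated amendment made before unblinding, replace the Bonferroni sentence under Statistical analysis with text such as: the two primary outcomes will be tested by Holm's step-down procedure at an overall two-sided 5%; the smaller p-value is compared with 0.025 and, only if it is significant, the larger with 0.05. Show a 97.5% confidence interval for each outcome, and state that it may include zero for an outcome passed at the 0.05 step.

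The cost is one sentence, the amendment record and that possible mismatch between interval and test. Recruitment and data collection do not change. If outcomes by arm have already been seen, keep the written rule as primary and label any Holm result as post hoc. Reconcile the 0.05 used for sizing with the 0.025 used for testing separately, since this change does not do so.

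### Separate unadjusted tests at 3 h and 24 h leave the preoperative and the other postoperative pain score unused; one joint model would gain a little power, and more if scores are lost in relation to pain

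*Protocol article*

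**What the plan says.** All references are to the protocol article.

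- **Primary outcomes:** "The primary outcome of interest is the dynamic pain score at 3 and 24 h postoperatively", on a scale from 0 to 10.
- **Statistical analysis, test:** the rule for scores that pass the normality check is "Normally distributed data will be displayed as mean ± standard deviation and analysed using unpaired", where the last word refers to the two-sample t-test. Scores that fail the check go to the Mann–Whitney test instead. Each score is compared on its own, without covariates.
- **Statistical analysis, principle and threshold:** "Intention to treat analysis will be performed in all cases". Each primary outcome is judged at a "value threshold of 0.025, obtained using the Bonferroni correction technique, will be utilised when assessing these outcomes".
- **Sample size calculation:** "Accounting for 30% dropout or non-adherence rate, we arrived at a final sample size of 35 in each arm".
- **Data collection and outcomes of interest:** a preoperative pain score is recorded before randomisation.
- **Patient population** and **Recruitment, enrolment and randomisation:** both expect high retention, because follow-up is short and in hospital.
- **Benefit and risks in participation:** participant request and uncontrollable pain are among the reasons for stopping or changing the allocated intervention.

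**The concern.** Each patient can supply three related pain scores: preoperative, 3 h and 24 h. The named tests use one at a time, with two consequences.

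First, variation that the preoperative score could explain stays in the error term, so some power is lost even when every score is present.

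Second, a two-sample test has no place for a patient without that score. Someone with a 3 h score but no 24 h score drops out of the 24 h comparison unless the score is imputed. If patients with more pain at 3 h are more likely to lose the 24 h score, and the arms differ at 3 h as the design assumes, those left in the two arms are no longer comparable. The 24 h difference is then biased, in a direction that depends on who is lost. Its false-positive rate can also exceed 0.025.

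**Working it through.** **1. The plan's own figure.** From 26 per group and 30%: 26 × 1.3 = 33.8, or 34; 26 / (1 − 0.3) = 37.1, or 38. The stated 35 fits the first within a patient or two. If all 30% were missing scores, 35 × 0.7 = 24.5 per arm would remain.

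**2. Implied effects.** The protocol gives no SD. Its sample size used a "two-sided significance level of 0.05 and 80% power". Solving the two-sample t-test gives a standardised difference of 0.792 at 3 h (26 per group) and 0.909 at 24 h (20 per group). The implied SDs are 0.8 / 0.792 = 1.01 and 3.3 / 0.909 = 3.63 points. All power figures below are at the planned 0.025.

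**3. Full retention.** Adjusting for a baseline score with correlation r multiplies the residual SD by √(1 − r²). The correlations are assumptions.
- 3 h, no adjustment: difference 0.792, 35 per arm, power 84%.
- 3 h, r = 0.3: 0.792 / √0.91 = 0.83, power about 88%.
- 3 h, r = 0.5: 0.792 / √0.75 = 0.91, power about 93%.

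At 24 h the unadjusted test already has about 93% power, so there is less to gain.

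**4. Where the bias comes from.** In SD units, the expected 24 h score is the arm mean plus ρ × (3 h score − arm mean at 3 h), where ρ is the 3 h to 24 h correlation. The bias of the observed-case difference is therefore ρ × (difference between arms in the mean 3 h deviation of those still observed). It is zero if ρ = 0, if loss is random, or if the arms do not differ at 3 h.

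**5. Power at 24 h.** Simulated with rounded scores bounded at 0 and 10, 35 per arm, baseline correlation 0.3, ρ of 0.3–0.6, a true 24 h effect of 0.91 SD and loss related to 3 h pain:

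| 24 h scores lost | t-test | Joint model | Gain (points) |
|---|---|---|---|
| none | 92–93% | about 94% | 1–2 |
| 10% | 86–88% | 91–92% | 3 (91 − 88) to 6 (92 − 86) |
| 30% | 72–74% | 81–86% | 7 (81 − 74) to 14 (86 − 72) |

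The joint model showed little bias and a false-positive rate near 2.5%.

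**6. Bias and false positives of the t-test.** Simulated with normal scores, a 0.8 SD difference at 3 h, ρ of 0.3–0.7, and log-odds of loss rising by 1–2 per SD of 3 h pain.
- 30% loss: bias 0.03–0.17 SD. In points this is 0.03 × 3.63 = 0.1 to 0.17 × 3.63 = 0.6, against a design difference of 3.3. The false-positive rate is 2.4–5.4%; a repeat run gave 2.6–4.8%.
- 10% loss: bias 0.01–0.09 SD, at most 0.09 × 3.63 = 0.3 points.

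**7. Limits of the joint model.** These runs used a separate set of normal-score simulations, with baseline correlation 0.3 unless noted.
- 30% random loss: neither method is biased. Power is 79–81% for the t-test and 82–88% for the joint model at ρ of 0.3–0.7. If all correlations were zero, the joint model would be slightly worse (78% against 80%).
- 30% loss that depends on the unseen 24 h score: t-test bias is about 0.21 SD. Joint-model bias is 0.18, 0.16 and 0.12 SD at ρ of 0.3, 0.5 and 0.7.
- 5% loss: t-test bias is about 0.04 SD or less when loss depends on 3 h pain. Across the loss mechanisms, power is 88–92% against 89–94%.

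**The case against.** The strongest reply is that this is a missing-data complaint under another name. Rules for missing scores usually sit in the analysis plan, which is not shown, and a t-test can be run after imputation. That stands: the absence of a rule is no finding, and the observed-case reading holds only if nothing is imputed. It does not touch the choice of test, which the article does fix and which leaves collected scores unused.

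A reader might infer that the tests contradict the intention-to-treat statement. They do not. The section contrasts intention to treat with non-adherence and a per-protocol analysis, so it means analysis by allocated arm, not that every randomised patient has a score.

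A reader might also infer that the plan expects 30% of scores to be missing. It does not. The allowance combines dropout with non-adherence, non-adherent patients keep their scores, and two sections expect high retention. Stopping the allocated intervention because of pain does not in itself mean a missing score either.

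It is also fair that the larger figures need several assumptions at once, none of them from the protocol. The 5.4% false-positive rate is one corner: 30% loss, ρ = 0.7, the steepest loss slope, a 0.8 SD effect at 3 h and none at 24 h. With random loss of the full 30%, the 24 h t-test still has about the planned 80% power. Finally, a normal-theory model for a bounded score in 70 patients is a modelling choice, although it held up on rounded, bounded scores.

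**Conclusion.** The point holds as a better available method, not as an internal contradiction. If retention is as high as expected, the gain is small: 1–2 percentage points of 24 h power with no loss and 3–6 at 10% pain-related loss, plus about 4 points at 3 h (84% to 88%) if the baseline correlation is 0.3. The 7–14 point gain is an upper bound tied to all 30% being missing 24 h scores.

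The documents do not support saying that a joint model would remove the bias. It does so if loss depends only on observed scores, and only reduces it if loss depends on the missing score itself. A patient with neither postoperative score adds almost nothing. Every correlation and loss mechanism here is assumed. The inflation formula, and sizing at 0.05 while testing at 0.025, are separate matters.

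**What to change.** Make the primary analysis one mixed model for repeated measures on the 3 h and 24 h scores, by randomised arm:

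- terms for arm, time, arm-by-time, and preoperative pain with its own slope at each time;
- unstructured covariance between the two times;
- every patient with at least one postoperative score included;
- the 3 h and 24 h arm contrasts each read at the planned 0.025.

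Keep the t-test or Mann–Whitney test as a supporting analysis labelled as observed cases. Add one sensitivity analysis that shifts the missing 24 h scores over a stated range. Fix all of this before unblinding, since a model chosen after the losses are known would carry less weight.

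The cost is a paragraph of analysis wording and a few lines of Stata 18 code, with no new data and no more patients. The price is reliance on a normal-theory model and on loss depending only on observed scores; the supporting and sensitivity analyses examine these. The article does not say whether the preoperative pain score is dynamic. That affects how much it explains, not whether it may be used.

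### A Shapiro–Wilk gate chooses the test for the two primary pain scores and will probably lead to a rank test, although the trial is sized on mean differences

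*Protocol article*

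**What the plan says.** Under Primary outcomes the protocol article states: "The primary outcome of interest is the dynamic pain score at 3 and 24 h postoperatively". On the scale it adds: "These scores are measured using a numerical pain scale from zero to ten".

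Under Sample size calculation both time points are sized on a difference in means, "with two-sided significance level of 0.05 and 80% power":
- 3 h: "The sample size required to detect a mean difference in pain scores of 0.8 at 3 h postoperatively was 26 in each group".
- 24 h: "detect a mean difference in pain scores of 3.3 at 24 h postoperatively was 20 in each group".

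The final figure is 35 per arm. No SD is given.

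Under Statistical analysis, the only provision specific to the primary outcomes is a Bonferroni threshold of 0.025 for each. The test comes from the general rule for continuous variables: "Continuous variables will be assessed for normality using the Shapiro–Wilk test". Data judged normal are summarised by mean and SD and compared by unpaired t-test. Otherwise: "Continuous data that is not normally distributed will be displayed as median (range) and analysed using" the Mann–Whitney U test. The section does not say whether normality is examined within each arm or in the pooled data.

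**The concern.** The trial's own data decide which hypothesis is tested on each confirmatory outcome. The t-test compares means. Mann–Whitney asks whether a score from one arm tends to exceed a score from the other. The two questions coincide only under extra conditions, for example when one distribution is a shifted copy of the other.

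The gate is also a poor guide. A 0–10 score recorded in whole numbers is discrete and bounded, so Shapiro–Wilk tends to reject for those reasons alone, whether or not a comparison of means is sound at this sample size.

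At stake is the link between the stated target and the primary result. The mean differences that justified the sample size may not be what the primary test addresses. The two primary time points may get different tests, and an unstated detail (by arm or pooled) can change the branch.

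**Working it through.** **1. Recovering the SDs.** For a two-sided, two-sample t-test with n per group, df = 2n − 2 and noncentrality d·√(n/2), where d = mean difference / SD. At alpha 0.05 and 80% power:
- 3 h: d = 0.80 gives power 0.807 at n = 26 and 0.791 at n = 25, so the stated 26 is reproduced when SD = 1.0. All d from 0.792 to 0.809 give n = 26, so SD lies between 0.8/0.809 = 0.99 and 0.8/0.792 = 1.01.
- 24 h: n = 20 requires d from 0.909 to 0.934, so SD lies between 3.3/0.934 = 3.53 and 3.3/0.909 = 3.63.

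These SDs are assumptions inferred from the stated sample sizes.

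**2. How often the gate rejects.** Scores were drawn from a normal distribution, rounded to whole numbers and clipped to 0–10, with 4,000 replicates per setting. Whole-number scoring is assumed. Shapiro–Wilk was applied at 0.05.

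| Setting (mean, SD) | n per arm | Rejects in at least one arm | Rejects pooled |
|---|---|---|---|
| 3 h, 2 v 2, SD 1 | 26 | 99.7% | 100% |
| 3 h, 2 v 2, SD 1 | 35 | 100% | 100% |
| 3 h, 4 v 3.2, SD 1 | 35 | 100% | 100% |
| 24 h, 5 v 5, SD 3.6 | 26 | 57.4% | 90.6% |
| 24 h, 5 v 5, SD 3.6 | 35 | 83.2% | 99.5% |
| 24 h, 6.5 v 3.2, SD 3.6 | 26 | 89.1% | 97.6% |
| 24 h, 6.5 v 3.2, SD 3.6 | 35 | 98.4% | 100% |

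Repeat runs at 35 per arm put the 24 h by-arm figure at about 80–98%.

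Because the 3 h outcome almost always goes to Mann–Whitney, the time points get different tests roughly whenever the 24 h gate passes. By arm, that is 100 − 98.4 = 1.6% to 100 − 83.2 = 16.8% of trials at 35 per arm, and 100 − 89.1 = 10.9% to 100 − 57.4 = 42.6% at 26 per arm.

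**3. Error rate and power of the rule, threshold 0.025.**
- Identical arms: the rule rejects in 0.024–0.026 of these trials at 35 per arm. Other runs gave 0.020–0.027. There is no inflation.
- 3 h, true shift 0.8, SD 1: at 35 per arm, t-test 0.812–0.819 against rule 0.790–0.804, a loss of about 2 points. At 26 per arm, 0.672–0.676 against 0.648–0.651, a loss of about 2.5 points.
- 24 h, nominal shift 3.3, SD 3.6: at 35 per arm, 0.927 against 0.920. Clipping shrinks the realised mean difference to about 2.7.

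**4. Equal means, different shapes (illustrative).** One arm is N(3, 1). The other is 80% N(2, 1) and 20% N(7, 1.5). Both are rounded. The second mean is 0.8 × 2 + 0.2 × 7 = 3.0, so the means are equal, but the medians are 3 and 2. At 35 per arm and threshold 0.025, the plan's route is significant in about 21–24% of trials, and an unequal-variance (Welch) comparison of means in about 3%. With a second pair of assumed shapes sharing a mean of 2.28, Mann–Whitney rejected in 33% (26 per arm) to 41% (35 per arm), against about 4% for the t-test. In both illustrations the gate essentially always chose Mann–Whitney.

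**The case against.** Several points on the other side stand.

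- **Error rate.** A reader might infer that choosing the test by a pre-test inflates the type I error. The simulations do not support this: with identical arms the rule stays near 0.025, and the cost in power is slight.
- **The equal-means figure.** The 21–24% might be read as a false-positive rate. It is not. In that illustration most patients in one arm have less pain, and the chance that a score in the first arm exceeds one in the second, counting ties as half, is about 0.60. Mann–Whitney is detecting a real difference in distribution. The shapes are assumed; nothing in the article indicates that they will occur.
- **Dependence on the data.** If the gate nearly always fails at 3 h, the 3 h test is in practice fixed, and both branches are written in advance. Genuine uncertainty about the branch is mostly at 24 h. This narrows the complaint about data dependence, but it makes the mismatch with "required to detect a mean difference in pain scores of 3.3" and with the 3 h target close to certain.
- **Effect estimates.** One might say that the plan forbids an effect estimate or confidence interval. It does not. The text describes how data will be displayed, the t-test branch names no interval either, and such detail is commonly left to a full protocol or analysis plan that is not shown.
- **Rank tests.** Mann–Whitney is a legitimate choice for a bounded pain score, and the outcome definition does not itself name a mean. Fixing it as the sole primary test would also remove the gate, but the sample size would then need to be justified on that basis.

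None of this answers the central point: the written rule governs the primary outcomes and probably leads to a test that does not address the difference used for sizing.

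**Conclusion.** The point holds as one about the estimand and its link to the sample size. The stated rule applies to both primary outcomes, because no other test is given for them. Under whole-number scoring and the back-solved SDs, it sends the 3 h score to Mann–Whitney in about 100% of trials and the 24 h score in about 80–98% at 35 per arm. At 26 per arm the 24 h by-arm figure falls to about 57–89%, so the branch there is less predictable.

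The consequence is a probable primary test that does not address the mean differences of 0.8 and 3.3, and possibly different tests at the two time points. The conclusion that a rank test is likely depends on the assumed score distributions. The mismatch in the written rule does not.

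**What to change.** Exempt the two primary outcomes from the normality gate. Prespecify one analysis at each time point: the difference in mean pain score between arms with a 97.5% CI (matching the 0.025 threshold), from an unequal-variance comparison such as a linear model with robust standard errors. Report Mann–Whitney with a Hodges–Lehmann estimate as a sensitivity analysis, whatever the shape of the data.

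The cost is a few sentences in the analysis section and slightly more analysis work, with no change to conduct or data collection. The article expected recruitment to finish in August 2025, so the change should be made and dated before the analysts see outcomes by allocation.

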## Methods

This is a multicentre triple-blinded pragmatic parallel design randomised controlled superiority trial that will be conducted at two teaching hospitals, Noarlunga Health Services (NHS) and Flinders Medical Centre (FMC), both located in Adelaide, Australia. We have obtained ethical approval from the relevant Human Research Ethics Committee prior to begin and shall obtain written informed consent from all participants. This study will conform to the recommendations of Consolidated Standards of Reporting Trials (CONSORT). All researchers have a current Good Clinical Practice certificate from within the last 3 years.

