### Data collection and outcomes of interest

Baseline demographic information including age, gender, ethnicity, body mass index, type of residence, chronic opioid usage, residence type, ASA grade, Charlson Comorbidity Index, preoperative patient reported outcome measures (Oxford Hip Score, EQ-5D-5L Index, pain score), preoperative mobility status and comorbidities will be collected prior to randomisation. The type of prosthesis used, as well as intraoperative complications will be recorded accordingly. Overall evaluation is expected to take approximately 30 min of the participants’ time. No compensation will be offered. Timing of data collection is shown in Fig. 1. Data entry into the password-protected trial database will be performed by trained research nurses and checked by senior investigators. In accordance with institutional policy, data will be stored for 15 years on the secure hospital server with access available to senior investigators.

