### Recruitment, enrolment and randomisation

Patient recruitment will be performed by a research nurse, who would identify potential participants, as well as screening them against the eligibility criteria. Informed consent would then be obtained by the research team following discussions about the expected benefits, risks, trial commitments and uncertainties of each technique. This is separate to the surgical consent for the procedure itself.

Computer-generated random treatment assignment (sealedenvelope.com) on a 1:1 ratio with permutated blocks (randomly generated blocks of 2, 4 and 6) will be performed immediately prior to surgery by the anaesthetist. Allocation concealment will thus be maintained. The intervention will be blinded to the patient, surgical and treating team, and the research team involved in data collection. Ward nursing staff shall also be blinded and shall be advised to treat all study patients as if they have had intrathecal morphine for safety reasons. Only the anaesthetist performing the intervention and their assistant shall not be blinded.

This is a pragmatic study designed for high external generalisability. All relevant concomitant care deemed necessary by the treating physicians will be permitted and recorded. Participant retention is by nature expected to be high in this RCT as it is short-term perioperative only.

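### The primary analysis leaves out the preoperative pain score collected before randomisation: the test is valid, but it gives up a small to moderate amount of precision

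*Protocol article*

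**What the plan says.** All references are to the protocol article.

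- **Outcome.** Under Primary outcomes: "The primary outcome of interest is the dynamic pain score at 3 and 24 h postoperatively", scored from 0 to 10.
- **Test.** Under Statistical analysis: "Normally distributed data will be displayed as mean ± standard deviation and analysed using unpaired" t-tests, and "Continuous data that is not normally distributed will be displayed as median (range) and analysed using" the Mann–Whitney test. No covariate and no adjusted analysis is named. Each primary outcome is tested at 0.025 after a Bonferroni correction.
- **Baseline data.** Under Data collection and outcomes of interest: "preoperative patient reported outcome measures (Oxford Hip Score, EQ-5D-5L Index, pain score), preoperative mobility status and comorbidities will be collected prior to randomisation". Chronic opioid use is in the same list.
- **Sites and allocation.** Methods says the trial "will be conducted at two teaching hospitals". Recruitment, enrolment and randomisation describes allocation "on a 1:1 ratio with permutated blocks (randomly generated blocks of 2, 4 and 6"), and does not say whether it was stratified by site.
- **Sample size.** 26 per group for a 0.8-point difference at 3 h and 20 per group for 3.3 points at 24 h, both at two-sided 0.05 and 80% power. Allowing for 30% dropout or non-adherence, the total is 35 per arm. No SD is given.

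**The concern.** The preoperative pain score is measured on every participant before allocation, so treatment cannot affect it. If it predicts postoperative pain, including it in the model removes that part of the outcome variance and allows for any chance imbalance between arms. The planned tests do neither. In a trial of 70 patients, with each primary outcome tested at 0.025, even a modest reduction in residual variance is useful and requires no further recruitment.

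The article names the test itself, so this is a comment on a stated choice and not on a detail left to an analysis plan that is not shown. The stakes are the width of the confidence interval and the power. Bias and type I error are not at issue.

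**Working it through.** **Inputs from the article.** Difference 0.8 points with 26 per group (3 h); 3.3 points with 20 per group (24 h); sizing at two-sided 0.05 and 80% power; testing at 0.025; 35 enrolled per arm; 30% allowance for loss.

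**Inputs that must be assumed.** The SD, and the correlation r between preoperative and postoperative pain. Neither is stated.

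**Step 1: the SD implied by the article's own figures.** Without an SD the stated sample sizes cannot be reproduced directly, so I solved for it, taking the calculation to be a two-sample t-test.

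- 3 h: 26 per group corresponds to a standardised difference of about 0.79 to 0.81, so SD = 0.8/0.81 to 0.8/0.79, about 0.99 to 1.01. Check: with SD 1.0 the t-test needs 25.5 per group, rounded up to 26.
- 24 h: 20 per group corresponds to about 0.91 to 0.93, so SD is about 3.53 to 3.63.

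**Step 2: effect of adjustment.** Adjusting for a baseline covariate multiplies the residual variance by (1 − r²), so the standardised difference becomes d/√(1 − r²). Power comes from the noncentral t distribution with noncentrality [d/√(1 − r²)] × √(n/2) and 2n − 3 degrees of freedom, one being spent on the covariate.

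Example with n = 26, d = 0.8 and level 0.025: the critical value is 2.312. The noncentrality is 0.8 × √13 = 2.884 at r = 0, giving 71.5%. At r = 0.3 it is (0.8/√0.91) × √13 = 3.024, giving 75.9%.

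**Step 3: power for the 3 h outcome at 0.025, SD 1.0.** The 24 per arm column is 35 × 0.7 = 24.5, rounded down.

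| r | 1 − r² | d/√(1 − r²) | 24 per arm | 26 per arm | 35 per arm |
|---|---|---|---|---|---|
| 0 (no gain) | 1.00 | 0.800 | 67.4% | 71.5% | 85.1% |
| 0.1 | 0.99 | 0.804 | 67.9% | 72.0% | 85.5% |
| 0.2 | 0.96 | 0.816 | 69.4% | 73.5% | 86.6% |
| 0.3 | 0.91 | 0.839 | 72.0% | 75.9% | 88.5% |
| 0.4 | 0.84 | 0.873 | 75.7% | 79.5% | 91.0% |
| 0.5 | 0.75 | 0.924 | 80.7% | 84.2% | 93.9% |

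The plain t-test has 2n − 2 degrees of freedom and differs from the first row by less than 0.1 point, so the covariate costs almost nothing even if it proves useless.

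**Step 4: the 24 h outcome.** With SD 3.63, d = 3.3/3.63 = 0.909. At 0.025, power with 26 per arm goes from 82.9% (r = 0) to 83.3% (r = 0.1) and 92.6% (r = 0.5). With 35 per arm it goes from 93.2% to 93.4% and 98.1%. There is less to gain here.

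**The case against.** The strongest reply is that nothing here is an error. An unadjusted comparison in a randomised trial is unbiased and keeps its type I error, and it matches a sample size apparently based on comparing two means. This stands. A reader might infer that the primary analysis is invalid or biased, and the documents do not support that.

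The size of the gain is also open to challenge. The baseline measure is listed among "preoperative patient reported outcome measures (Oxford Hip Score, EQ-5D-5L Index, pain score") and is not described as a dynamic score. It records pain before hip replacement, whereas the outcome is pain hours after surgery under spinal anaesthesia, with local infiltration in all patients and analgesics as needed. A weak correlation is plausible, particularly at 3 h, and at r = 0.1 the gain with 26 per arm is about 0.5 points. This stands too, and is why the range starts at 0.1.

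The 26-per-arm case is also the less favourable one. The article expects high retention and specifies intention to treat, so non-adherent patients stay in the analysis and the number analysed may be close to 35 per arm. Unadjusted 3 h power is then already about 85%. Moreover, the low figure at 26 per arm arises because the trial was sized at 0.05 and is tested at 0.025. That is a separate matter and should not be counted as a cost of omitting the covariate.

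Finally, a reader might infer from "permutated blocks (randomly generated blocks of 2, 4 and 6") and the two hospitals that allocation was unstratified and that omitting site is a fault. A condensed article that does not mention stratification does not show that there was none. If there was none, the design does not require a site term. The documents give no figure from which a gain for site or for chronic opioid use could be calculated.

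What survives is narrower. A pre-randomisation measure of the same kind of quantity as the outcome is available, using it costs very little, and the article fixes an analysis that leaves it out.

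**Conclusion.** The point holds as one of efficiency, limited to the preoperative pain score. The planned tests are valid but give up some precision. For the 3 h outcome at the 0.025 level, adjustment would raise power by about 0.5 to 13 percentage points with 26 analysable per arm (72.0 − 71.5 to 84.2 − 71.5), and by about 0.4 to 9 points with 35 per arm (85.5 − 85.1 to 93.9 − 85.1). Both ranges rest on an SD of about 1.0, which is back-solved and not stated, and on an assumed correlation of 0.1 to 0.5. If the true correlation is near the lower end, the gain is negligible. The figures support an inexpensive improvement to the plan. They do not support a claim that the trial's conclusions would be unsound without it, nor any claim about the size of a gain from adjusting for site or opioid use.

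**What to change.** Before unblinding, amend the analysis text as follows.

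1. For each primary time point, make the primary analysis a linear regression (ANCOVA) of pain score on arm, adjusted for preoperative pain score. Report the adjusted mean difference with a 97.5% confidence interval, which matches the 0.025 threshold. If robust standard errors are used, choose a version with a small-sample correction, since uncorrected ones can be too small with around 50 patients.
2. State a simple rule for missing baseline scores, for example replacing them with the overall baseline mean across both arms, so that no randomised patient with an outcome is lost.
3. Keep the unadjusted comparison as a sensitivity analysis.
4. Include a site term if randomisation was in fact stratified by site; otherwise it is optional. In either case say so in advance. Any further covariate, such as chronic opioid use, should be named now or left out, because adding one after seeing an imbalance would be data-driven.

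The cost is a few sentences in the analysis section, one degree of freedom per model and the missing-baseline rule. No new data or patients are needed.
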